### Blinding

Investigators and participants will remain blinded throughout the trial. Emergency unblinding will be allowed in limited situations that impact on the safety of study participants. Code-break envelopes for the full randomization schedule will be maintained by the Leeds General Infirmary pharmacy, and pharmacies at other sites will hold code-break envelopes for their respective participants. A 24-hour code-break telephone line will also be established in case of the need for emergency out-of-hours unblinding. Participants who are unblinded will be withdrawn from treatment but will continue to be followed as per the planned follow-up schedule, unless they request to fully withdraw from the trial.

#### Maintaining the treatment blind

Given the possible toxicities related to MTX, there is potential for investigators reviewing blood results to become aware of treatment. Therefore, patient-reported outcomes will be completed before any changes in dose or results of blood monitoring are discussed with participants. Where possible, members of staff with knowledge of blood results will not be responsible for administering patient questionnaires.

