### Trial development

The trial was designed with key stakeholders including rheumatologists with experience of treating OA, general practitioners with a special interest in musculoskeletal disease, methodologists and users with experience of knee OA. The intention was to be pragmatic, allowing physicians to include MTX in the overall care of patients with knee OA and have relative flexibility in this regard, thereby being representative of clinical practice. We faced a number of challenges in achieving the ideal design for the PROMOTE trial which are discussed in more detail in the relevant sections below. Key challenges included defining the dosing and dose escalation strategy for use of MTX in OA patients, maintaining the blind due to the well-known side-effect profile of MTX, timing of the primary outcome, ensuring optimal recruitment for a trial that is conducted in secondary care for a condition where patients predominantly reside in primary care and maintaining the pragmatic nature of the trial with respect to concomitant medication use, whilst protecting the validity of the primary pain outcome.

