#### Clinical outcome measures

The primary endpoint of the study will be change in ‘average overall knee pain severity over the previous week’ (as graded on a zero to 10 numerical rating scale (NRS)) between baseline and six months (24 weeks). An NRS was chosen to measure pain as they have been found to be reliable and to demonstrate good face and criterion validity, and they are recommended as a core outcome measure for chronic pain clinical trials by the Initiative on Methods, Measurement, and Pain Assessment in Clinical Trials (IMMPACT) [46-50].

The timing of the primary outcome at six months was defined due to the slow-acting nature of MTX. Studies in RA have found that several months of treatment may be required before any symptomatic effect is noted [43,44]. Our own recent study of MTX versus MTX plus etanercept in RA, in which the MTX arm used the same dosing schedule as that planned for the PROMOTE trial, found that approximately 20% of participants in the MTX arm showed a major clinically significant response (tender and swollen joint count of zero) at three months, with this rising to 29% at six months and 33% at 12 months. In our pilot study of MTX in OA, the reduction in 48-hour pain VAS scores was significantly greater at 24 weeks (median (interquartile range (IQR)) reduction of 27 mm (four to 38)) than at 12 weeks (median (IQR) reduction of 9 mm (−1 to 36)).The dose escalation schedule for the PROMOTE trial requires a minimum of six weeks to reach maximum dosage, and in reality we know that it can often take longer than this to escalate the dosage. Taken together with evidence from the RA literature, which suggests that at least two to three months may be required at maximal dose for symptomatic benefit to be achieved, a primary outcome earlier than six months may fail to fully capture the clinical response to treatment. However, additional outcomes will be recorded at three months (12 weeks) to identify early response, and nine and 12 months (36 and 48 weeks) to capture longevity of response.

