#### Blood and urine safety assessment

Safety of therapy will be assessed according to regional monitoring guidelines and will be determined by treatment strategy. Full blood count (FBC), liver function test (LFT) and urea and electrolytes (U&E) tests will be performed at screening, every two weeks for the first eight weeks, and every four weeks thereafter. If a patient’s results remain abnormal despite action (such as reducing their MTX dose), or at clinician discretion, then study medication will be stopped. For the purposes of this study, abnormal is defined as: haemoglobin ≤8.5 g/dL; white cell count (WCC) ≤3.5 × 10^9^/L; neutrophils ≤1.5 × 10^9^/L; platelets ≤100 × 10^9^/L; alanine aminotransferase (ALT) > two times the upper limit of normal (ULN) for the laboratory conducting the test; creatinine >1.5 times the ULN for the laboratory conducting the test and estimated glomerular filtration rate (eGFR) <30 mL/minute.

C-reactive protein (CRP), anti-cyclic citrullinated protein (anti-CCP) and rheumatoid factor (RF) tests will be performed at screening. Anti-CCP and RF results from the previous 12 months may be used if these are available. A dipstick urinalysis will be performed at screening to check for evidence of leucocytes, blood or protein, to exclude urine infection. A urine dipstick pregnancy test will be performed for female participants with child-bearing potential, and appropriate contraceptive methods documented for those at risk.

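### The rule that protects the blind puts questionnaires ahead of dose and blood-result discussion but not ahead of the adverse-event enquiry, although side effects are the threat the article names

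*Protocol article*

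**What the plan says.** Under Trial development, the article counts "maintaining the blind due to the well-known side-effect profile of MTX" among its key design challenges and says these are taken up in later sections. The later section, Maintaining the treatment blind, narrows the risk to laboratory data: "there is potential for investigators reviewing blood results to become aware of treatment". It gives two measures. The first is an order of events: "patient-reported outcomes will be completed before any changes in dose or results of blood monitoring are discussed with participants". The second is staff separation: "Where possible, members of staff with knowledge of blood results will not be responsible for administering patient questionnaires".

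The Blinding section states that "Investigators and participants will remain blinded throughout the trial".

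Table 2 ticks the primary 0 to 10 pain rating, adverse events and concomitant medication at months 3, 6, 9 and 12. A footnote adds adverse events and concomitant medication at months 1 and 2. Safety bloods are taken at screening and then "every two weeks for the first eight weeks, and every four weeks thereafter". The primary time point is six months, given as 24 weeks.

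**The concern.** The primary outcome is the participant's own rating, so what the participant believes about allocation can affect it. The article names side effects as the threat, then writes an ordering rule that covers two other topics. A conversation about nausea, headache or lethargy just before the pain question could bring a suspected allocation to mind at the moment of measurement, and the stated rule does not prevent it.

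The rule is also local to one visit. By month 6 a participant may already have had side effects, an abnormal result or a dose reduction, and the order of events on that day cannot undo this.

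If such cues are more common on methotrexate, and if they lead people to report less pain, the treatment difference would be inflated. Both conditions are plausible. Neither is quantified in the documents.

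**Working it through.** **1. What the rule covers, set against what happens at the visit**

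| Item at the month-6 visit | Scheduled in | Must follow the questionnaires? |
|---|---|---|
| Discussion of dose changes | Dosing section | Yes |
| Discussion of blood results | Blood and urine safety assessment | Yes |
| Adverse-event recording | Table 2 | Not stated |
| Concomitant-medication recording | Table 2 | Not stated |

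The last two rows are the gap. The staff-separation measure does not close it: it applies where possible, and it concerns knowledge of blood results, not enquiry about side effects.

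**2. What precedes the six-month score**

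The monitoring schedule gives on-treatment blood rounds at weeks 2, 4, 6, 8, 12, 16, 20 and 24. Seven of them (weeks 2, 4, 6, 8, 12, 16 and 20) fall before week 24. The screening sample precedes treatment and cannot hint at the arm. These seven are occasions on which an abnormal result could become known. They are not seven disclosures: the schedule is the same in both arms, and a normal result reveals nothing. The planned dose steps are likewise written for methotrexate or placebo alike. Only side effects, abnormal results and the actions that follow them can point to an arm.

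**3. Can the effect be sized?**

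The blinding sections state no figure to reproduce. A calculation needs two inputs that the documents do not give: the excess share *f* of the methotrexate arm that infers its allocation, and the shift *s* in pain rating that follows. The spurious difference is *b* = *f* × *s*. Purely as assumptions:

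- Low: *f* = 10%, *s* = 0.5 gives *b* = 0.10 × 0.5 = 0.05 points.
- High: *f* = 50%, *s* = 2 gives *b* = 0.50 × 2 = 1.0 point.

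With 64 per arm, SE = SD × √(2/64). That is 0.71 at the planning SD of 4, and 0.42 at 2.4, the larger of the two change SDs cited under Sample size. The false-positive probability is 1 − Φ(1.96 − *b*/SE) + Φ(−1.96 − *b*/SE). From the low to the high assumption it runs from 5.1% to 29% at SD 4, and from 5.2% to 65% at SD 2.4, against a nominal 5%. The range goes from negligible to serious and is set entirely by the assumed inputs. It supports no statement about this trial's bias.

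**The case against.** The strongest reply is that the article promises less than a reader might infer, and does more.

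- **No guarantee is given.** The ordering rule answers a stated and narrower risk, that of investigators inferring the arm from blood results. The Blinding section describes who is kept blind. Neither says that the six-month score is free of participant inference, so it would be wrong to say that the score is not protected as claimed. This stands.
- **Other measures exist.** Capsules are identical, all participants receive folic acid to ease side effects, there is no switch to subcutaneous dosing because of the blind, and staff are separated where possible. These reduce the risk. None of them sets the order of the adverse-event enquiry.
- **The article is condensed.** Visit order may be fixed in the full protocol or a site manual, and a question on believed allocation may sit in forms not shown. Its absence from Table 2 is therefore no finding. The ordering rule is different: the article states it explicitly and lists what it covers.
- **A pilot-based estimate fails.** A reader might take the pilot's four side-effect withdrawals and four dose reductions as 7 to 8 of 30 (23% to 27%), depending on overlap, assume a 1-point shift, and obtain 0.23 to 0.27 points. That is about a third of the 0.73 to 0.83 needed for significance at SDs of 2.1 to 2.4. The pilot was open-label with no placebo arm, so this is not a between-arm excess. Withdrawn patients are counted against a sample size that is net of dropout. The planning SD of 4 raises the threshold to 1.96 × 4 × √(2/64) = 1.39. The 1-point shift has no source.
- **Reordering is a partial remedy.** Participants know their own side effects whatever the order. This stands, and it limits what the fix can claim.

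**Conclusion.** The point holds in a limited form. The article identifies side effects as a threat to the blind, and its ordering rule leaves out the enquiry about them, which is scheduled at the same visits as the primary pain rating. The rule limits information given at a visit. It does not reach what participants have already noticed or been told.

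This is a low-cost improvement to a stated rule, not evidence that the primary result will be biased. No magnitude should be attached to it, because the documents contain no by-arm rate of allocation cues and no expectation effect. That any bias would favour methotrexate is a reasonable expectation but remains an assumption. The sample size and planned analysis are unaffected. The conclusion assumes that no fuller document already fixes the visit order; if one does, the article's wording only needs to match it.

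**What to change.** Extend the ordering rule under Maintaining the treatment blind: at every visit the patient-reported outcomes, with the primary pain rating first, are completed before the adverse-event enquiry and the medication review, as well as before dose or blood results are discussed. It would help to add that the rule limits prompting at that visit only.

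The cost is one instruction to sites, with no new visit, staff or data item. As the article reports recruitment begun and follow-up in progress, it would apply to the remaining visits in both arms.

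A question on believed allocation, with the main reason, is optional. Month 3 may look like the natural time, since the article argues that "at least two to three months may be required at maximal dose for symptomatic benefit to be achieved" and an early guess might then reflect mainly side effects. But the article also measures at three months to pick up early response, and its pilot reports a median fall of 9 mm at 12 weeks, so a month-3 guess could reflect efficacy. Asking then could also prompt guessing before the primary endpoint. If the item is used, it is better placed after the six-month primary rating and reported by arm as description. It cannot by itself separate drug effect from unblinding.

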### Data collection

All data will be collected on standardized CRFs, which will be completed by site staff, verified by the principal investigator, and returned to the clinical trials unit for data entry. Study sites will also return a patient non-identifiable participant log and study drug dispensing log to the clinical trials unit.

#### Patient reported, clinical and imaging assessments

In addition to the patient-reported measures of pain, function and quality-of-life and imaging outcome measures described above and outlined in Table 2, a number of additional data elements will be collected during the trial. At the baseline visit, medical history and demographic data, including smoking and alcohol consumption, employment and family history of knee OA will be collected. Physical examination and vital signs, including height and weight, will be collected at screening, six and 12 months. A clinical examination of the knee will also be conducted at the baseline visit. This will assess effusion on a zero to three scale, where one is positive bulge sign, two is positive fluctuance (balloon sign) and three is tense effusion, and compartmental (medial tibiofemoral (MTF), lateral tibiofemoral (LTF) or patellofemoral (PF)) tenderness, also measured on a zero to three scale. The specific tools used to capture each data element are further detailed in Table 2.

#### Safety assessments

Adverse events will be recorded throughout the study. Intensity and relationship to the study medication will be ascribed.

#### Blood and urine safety assessment

Safety of therapy will be assessed according to regional monitoring guidelines and will be determined by treatment strategy. Full blood count (FBC), liver function test (LFT) and urea and electrolytes (U&E) tests will be performed at screening, every two weeks for the first eight weeks, and every four weeks thereafter. If a patient’s results remain abnormal despite action (such as reducing their MTX dose), or at clinician discretion, then study medication will be stopped. For the purposes of this study, abnormal is defined as: haemoglobin ≤8.5 g/dL; white cell count (WCC) ≤3.5 × 10^9^/L; neutrophils ≤1.5 × 10^9^/L; platelets ≤100 × 10^9^/L; alanine aminotransferase (ALT) > two times the upper limit of normal (ULN) for the laboratory conducting the test; creatinine >1.5 times the ULN for the laboratory conducting the test and estimated glomerular filtration rate (eGFR) <30 mL/minute.

C-reactive protein (CRP), anti-cyclic citrullinated protein (anti-CCP) and rheumatoid factor (RF) tests will be performed at screening. Anti-CCP and RF results from the previous 12 months may be used if these are available. A dipstick urinalysis will be performed at screening to check for evidence of leucocytes, blood or protein, to exclude urine infection. A urine dipstick pregnancy test will be performed for female participants with child-bearing potential, and appropriate contraceptive methods documented for those at risk.

### Data integrity and management

All data obtained will be kept strictly confidential and will be stored electronically on a database with secured and restricted access. Datasets for each subject will be identified by the participant trial identification number only.

### Withdrawal

All participants have the right to withdraw consent at any time without prejudice. At the time of withdrawal of consent, a full efficacy and safety evaluation should be performed if the participant consents. Participants who withdraw will be asked to complete the questionnaires as per the next planned study visit. At a participant’s request, their data collected up to the point of withdrawal can also be withdrawn from the trial and will not be used in the final analysis. Participants who withdraw will return to routine care in the rheumatology and musculoskeletal out-patient clinics.

In the event that a patient is unable to tolerate 7.5 mg of MTX, they will be withdrawn from treatment but will continue to be followed up on as per the planned follow-up schedule, unless they request to fully withdraw from the trial.

### Study site staff training

A centralized introduction and training session was held for all principal investigators and site staff. In addition to this, a site initiation visit will be held at all sites, in order to provide specific training to all staff involved in the study ahead of recruitment. Pre-study training will be conducted to ensure robustness of MRI acquisition.

### Trial site monitoring

The trial will be overseen and monitored by the York Trials Unit on behalf of the Sponsor, the University of Leeds. Each site will be assessed prior to site setup, and visited again once the third participant is recruited or at 20 weeks after the start of recruitment at site, whichever is sooner. The PROMOTE trial was assessed as low risk by the Medicines and Healthcare Products Regulatory Agency (MHRA), and therefore in addition to the single monitoring visit, procedures for central monitoring at the clinical trials unit have been put in place. This will mainly involve cross-checking logs returned from the research team and site pharmacy for consistency. A data monitoring and ethics committee will provide independent oversight to ensure data quality and compliance with the trial protocol.

### Statistical analysis

Full details of the statistical methods will be written in an approved statistical analysis plan prior to any data analysis.

### Primary endpoint analysis

The primary analysis will be conducted on the intention-to-treat population, including all randomized participants in the groups to which they were randomized. A per protocol population (excluding major protocol violations) will be used to check the robustness of the primary analyses. The safety population will consist of all patients receiving at least one dose of the study drug.

The first 30 participants (included in the internal pilot study) will be included in the main trial analysis along with the rest of the participants. Wittes and Brittain show that sample size re-estimation using an internal pilot study has minimum impact on the overall type I error, therefore an alpha level of 0.05 will still be used for the primary analysis [57].

The pilot phase analysis, which will be conducted after primary outcome data becomes available for the thirtieth participant, will include the following:Assessment of the variability of the primary outcome measure, the estimate (SD) will be used to update the sample size calculation;Consent rate (out of the number of information packs sent out during the pilot phase);Retention rates associated with each treatment andReturn rate for the six-month outcome assessment.

The primary analysis for the main study will be conducted using linear regression adjusting for the baseline measure. Treatment groups will be compared at six months with respect to their average overall knee pain severity over the previous week.

All secondary analyses will be conducted using linear or logistic regression, depending on the type of outcome measure, adjusting for the same covariates as the primary analysis. The intention-to-treat population will be used for all secondary analyses. All secondary outcomes will be described descriptively (mean, SD, median, minimum and maximum for continuous data and counts and percentages for categorical data). The Short Form-12 questionnaire will be summarized for all components. To minimise multiple testing, only the overall physical component score and mental component score will be analysed, using the same analysis methods as for the primary outcome. For continuous outcomes the regression model assumptions will be checked and, if necessary, data will be transformed prior to analysis if this improves the model fit, or normalises the distribution of residuals.

Adverse events will be coded according to the MedDRA adverse event dictionary. The overall incidence of serious adverse events and adverse events and number and proportion of patients reporting such events will be summarized by treatment group. Adverse events (including serious adverse events) will be summarized by the number and percentage of subjects who experienced the event by system organ class and preferred term. Subjects will only be counted once. If a subject reports the same adverse event more than once then the maximum grade and strongest causal relationship to study treatment will be used for the summary tables. Adverse events will also be summarized by severity and by relationship to study drug. All adverse events will be included in individual subject line listings.

Analysis of MRI endpoints will be exploratory. Treatment groups will be compared with respect to changes in synovitis, cartilage and bone using linear regression models with adjustment for the same covariates as the primary analysis. Linear regression models will also be used to explore the association between symptom outcome and baseline MRI measurements. Changes in MR features and the relationship of these changes with symptom changes will be explored descriptively.

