#### Concomitant medication

In order to maintain the pragmatic nature of the trial, there are no restrictions written into the protocol with regard to concomitant analgesic medications. All participants, whether on MTX or placebo, will be allowed to continue taking the treatments for knee OA that they are taking at their screening visit for the duration of the trial. Investigators will be responsible for the overall management of a participant’s medication, and will ask participants to avoid changing their analgesic or anti-inflammatory medication for the duration of the trial. However, if a participant is experiencing increased pain and requires an increase in the dose of analgesics then the use of paracetamol, topical or oral NSAIDs or opioids, or a combination of these will be permitted, but the reason for the dose increase and the dose used will be documented. The choice of medications and doses to be used lie with the principal investigator and clinicians working at study sites in order to ensure that treatment for participants in both groups is optimized. Participants will be permitted to continue current use of chondroitin and glucosamine, provided the dose has been stable for three months at study entry; however their use must be clearly documented in the case report form (CRFChondroitin or glucosamine therapy will not be commenced during the duration of the trial. Chronic NSAID and opioid use days in the last three months) will be included as a covariate in the analysis.

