### Eligibility criteria

Participants must meet the inclusion and exclusion criteria (shown in Table 4) in order to participate. These will be assessed at the screening visit (Figure 2). Potential participants who are deemed ineligible at screening will be allowed a second screening visit if the reason for ineligibility is a temporary status (for example, recent corticosteroid injection; Table 4).

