**Table 4 Tab4:** **Eligibility criteria**

**Inclusion criteria**	**Exclusion criteria**
Fulfil clinical ACR Criteria for knee OA	The presence of any inflammatory arthritis (such as gout, reactive arthritis, rheumatoid arthritis, psoriatic arthritis, seronegative spondyloarthropathy, previous diagnosis of pseudogout in target joint with proven crystals on joint aspiration or elevated CRP at time of knee arthritis flare) or fibromyalgia.
Knee pain on most days in the last 3 months	
Knee pain is the predominant pain condition	Use of intra-articular (IA) hyaluronic acid in the signal knee within the 4 months preceding enrolment in the study^a^
Insufficient pain relief from, inability to tolerate or contra-indication to oral and/or topical NSAIDs and/or opioids. Moderate to severe pain of the signal knee as defined by a score of ≥40 mm on a VAS (0 to 100 mm) using the question ‘On average, how would you rate your knee pain during the last 3 months?’.	Use of IA, IM (intra-muscular) or oral corticosteroids in the 3 months preceding enrolment^a^
	Use of other anti-synovial agents (such as hydroxychloroquine or sulphasalazine) in the 2 months preceding the study^a^
	Significant knee injury or any knee surgery within the 6 months preceding enrolment in the study^a^
Patient able to identify a ‘signal’ painful knee (either the most painful knee or selected from equally painful knees)	The presence of non-OA causes of pain in the signal knee, such as referred hip pain, osteonecrosis or radicular spinal pain
A previous radiograph (X-ray) of the signal knee within the last 2 years with changes consistent with tibiofemoral OA	Commencement of physiotherapy or non-pharmacological knee OA treatment in the 2 months preceding the study^a^
No change in the average weekly dose of oral or topical analgesics (including NSAIDs) for at least 4 weeks^a^	A history of partial or complete joint replacement surgery in the signal knee at any time, listed for knee surgery or anticipating knee surgery during the study period
Has used chondroitin or glucosamine for at least 3 months with no change to the average weekly dose, is not using or is willing to stop using if recently started^a^	Women who are pregnant, breast-feeding or men or women planning pregnancy within 18 months after screening (approximately 6 months following last study medications)

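### The screening three-month knee-pain VAS is named in no model covariate set, so a nearly free and possibly small gain in precision is passed over

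*Protocol article*

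**What the plan says.** The primary endpoint is the change in past-week average knee pain on a 0 to 10 NRS from baseline to six months (Clinical outcome measures). Under Primary endpoint analysis, "The primary analysis for the main study will be conducted using linear regression adjusting for the baseline measure". The same section has the secondary models "adjusting for the same covariates as the primary analysis", in the plural. Under Concomitant medication, days of chronic NSAID and opioid use over the last three months "will be included as a covariate in the analysis", without saying which analysis.

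Table 4 requires "Moderate to severe pain of the signal knee as defined by a score of ≥40 mm on a VAS (0 to 100 mm", with the question "On average, how would you rate your knee pain during the last 3 months". Of the eligibility criteria, the text says "These will be assessed at the screening visit". Nothing in the article uses this VAS beyond the entry threshold, and Table 2 (outcome measures) does not list it.

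**The concern.** A single past-week rating is an imperfect measure of a patient's usual pain. The screening VAS asks about the same construct over a longer period and on a different scale, and each eligible participant answers it before randomisation. In a linear model, a second pre-randomisation score leaves the treatment contrast and its interpretation unchanged. It can remove some residual variance and correct chance imbalance in usual pain that the one-week score misses. At stake is the width of the confidence interval for the primary comparison. Because the secondary models take over the primary covariates, the other pain outcomes could gain as well.

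**Working it through.** **1. The plan's own sample size.** Inputs from the Sample size section: difference 2 points, SD 4, 80% power, 5% significance (two-sided assumed), 20% dropout.

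- Normal approximation: n = 2 × (1.96 + 0.84)² × 4² / 2² = 62.8, so 63 per arm.
- Exact t-test: 64 per arm (power 80.1%).
- Total: 128 / 0.8 = 160.

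The stated figures reproduce. The calculation uses no covariate, so leaving out the VAS does not make it wrong.

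**2. Gain from a second baseline score.** Let r1 be the correlation of baseline NRS with six-month NRS, r2 that of screening VAS with six-month NRS, and r12 that of the two baseline scores. None is given in the documents; all values below are assumptions.

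- Residual variance with NRS alone: 1 − r1².
- With both: 1 − (r1² + r2² − 2·r1·r2·r12) / (1 − r12²).
- Proportional reduction: (r2 − r1·r12)² / [(1 − r1²)(1 − r12²)].

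With all three at 0.5, residual variance goes from 0.750 to 0.667. The reduction is 0.25² / (0.75 × 0.75) = 11.1%, which is 5.7% off the standard error.

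| r1 | r2 | r12 | Reduction in residual variance |
|---|---|---|---|
| 0.4 | 0.4 | 0.4 | 8.2% |
| 0.5 | 0.5 | 0.5 | 11.1% |
| 0.6 | 0.6 | 0.6 | 14.1% |
| 0.5 | 0.5 | 0.7 | 5.9% |
| 0.5 | 0.4 | 0.5 | 4.0% |
| 0.5 | 0.4 | 0.7 | 0.7% |
| 0.5 | 0.3 | 0.6 | 0.0% |

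The gain is nil whenever r2 = r1 × r12, as in the last row (0.5 × 0.6 = 0.3). If r1 and r2 each range over 0.4 to 0.6 and r12 over 0.5 to 0.7, the reduction spans about 0 to 25%, or about 3 to 19% when r1 = r2.

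**3. Effect of the 40 mm cut-off.** Truncating the VAS shrinks its variance to a fraction v but leaves the regression on both scores unchanged, so the two-covariate residual stays at 0.667. With all correlations 0.5 before truncation, baseline and six-month NRS each have variance 1 − 0.25(1 − v), and their covariance is 0.5 − 0.25(1 − v).

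- Cut-off one SD below the VAS mean (v = 0.630): NRS-only residual = 0.907 − 0.407² / 0.907 = 0.724; reduction = 1 − 0.667 / 0.724, about 8%.
- Cut-off at the VAS mean (v = 0.363): NRS-only residual = 0.841 − 0.341² / 0.841 = 0.703; reduction = 1 − 0.667 / 0.703, about 5%.

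The documents do not say where the cut-off falls in the VAS distribution, so this too is assumed.

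**4. What it means for the trial.** Reading SD 4 as the SD after adjustment for baseline NRS (normal approximation):

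| Reduction | n per arm for 80% power | Power at 64 per arm |
|---|---|---|
| 0% | 63 | 80.7% |
| 5% | 60 | 82.7% |
| 8% | 58 | 83.9% |
| 11% | 56 | 85.0% |

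The Sample size section calls SD 4 conservative and cites within-group change SDs of 2.1 and 2.4. At those values, power for 2 points with 64 per arm is already 99.97% and 99.7%. The benefit is then only a narrower interval: at SD 2.4, the 95% half-width is 1.96 × 2.4 × √(2/64) = 0.83 points, and an 8% cut in variance gives 0.83 × √0.92 = 0.80.

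**The case against.** The strongest reply is that nothing here is wrong. Regression adjusted for the baseline value of the outcome is standard and valid, and the article leaves full statistical detail to a SAP that is not shown, which may already include the VAS. That stands as to severity. It does not remove the point, because the article does state a covariate for the primary model rather than leaving the choice open.

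A reader might infer that the model adjusts for baseline NRS and nothing else. The documents do not support that: the Concomitant medication section names a further covariate, Primary endpoint analysis speaks of covariates in the plural, and the Abstract announces multivariable modelling. What can be said is that the VAS is not named, and that the places describing the covariate set do not line up.

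A reader might also infer that the mm value is already on file for everyone. The article makes the VAS an entry criterion but does not say that the score itself goes into the CRF, so this has to be checked.

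The VAS is also not the only candidate. Table 2 lists worst-pain NRS, WOMAC pain and ICOAP at month 0. That is fair; the case for the VAS is its longer recall period and its origin at screening, and the documents do not show that it would predict best.

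Finally, the gain rests wholly on assumed correlations and may be zero. This stands. If the SD is larger than expected, the internal pilot can raise recruitment anyway.

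**Conclusion.** The point holds as a missed, nearly free refinement of the primary model. The stronger inferences, that the planned analysis is biased, that the trial is underpowered, or that a known amount of precision is lost, have no support in the documents. With all correlations at 0.5 the reduction in residual variance is about 11%, and about 5 to 8% allowing for the entry cut-off; it falls to nil if the VAS adds nothing to the baseline NRS. These figures assume jointly normal scores and a cut-off between the VAS mean and one SD below it. Importance is low: worth doing because it costs so little.

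**What to change.** Before unblinding, state the primary model in the SAP as six-month NRS on arm, adjusted for baseline NRS and the screening three-month VAS as a continuous score in mm. In the same statement, settle whether NSAID and opioid use days belong to the primary model, so that Primary endpoint analysis and Concomitant medication agree. Confirm that the CRF holds the VAS in mm and not only pass or fail. Keep the recruitment target at 160 and do not bank the gain. The cost is one degree of freedom, a line of SAP text and a CRF check; the worst outcome is no gain.
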